**Patient**														
		Unplanned readmissions^a^										✓		✓
		Complications (sensitive to fundamental care activities)^a,b,c^										✓		✓
		First aid visit^a^										✓		✓
		ICU^d^ admission^a^										✓		✓
		EQ-5D-5L			✓				✓			✓		✓
		HADS^e^			✓				✓			✓		✓
		NRS^f^ patient satisfaction							✓					
		NRS sleep quality					✓							
		LOS^g^							✓					
		Bodyweight (in kilogram)			✓				✓			✓		✓
		Professional home care (indications)							✓			✓		✓
		SNAQ^h^			✓							✓		✓
		Braden scale			✓							✓		✓
		DOS^i^			✓		✓					✓		✓
		AMEXO^j^					✓					✓		✓
		JHFRAT^k^			✓							✓		✓
**Family caregiver**														
	**Objective burden**													
			Duration of informal care	✓				✓			✓		✓	
			Intensity of informal care	✓				✓			✓		✓	
			Health of patient	✓				✓			✓		✓	
			Need for permanent surveillance	✓				✓			✓		✓	
			Patients’ living situation	✓				✓			✓		✓	
			Use of professional care	✓				✓			✓		✓	
	**Subjective burden**													
			CSI+^l^	✓				✓			✓		✓	
			Self-rated burden scale	✓				✓			✓		✓	
			Perseverance time					✓			✓		✓	
	**Well-being**													
			CarerQoL-7D^m,n^	✓				✓			✓		✓	

^a^Unplanned readmissions, complications, first aid visits, and ICU admissions will be measured 30 and 90 days after surgery.

^b^Complications will be classified according to the revised version of the Clavien-Dino classification system.

^c^Complications sensitive to fundamental care activities: pneumonia, urinary tract infection, wound infection, deep vein thrombosis, malnutrition, and delirium.

^d^ICU: intensive care unit.

^e^HADS: Hospital Anxiety and Depression Scale.

^f^NRS: numeric rating scale.

^g^LOS: length of stay.

^h^SNAQ: Short Nutritional Assessment Questionnaire score.

^i^DOS: delirium observation scale.

^j^AMEXO: Amsterdam UMC Extension of the John Hopkins Highest Level of Mobility scale score.

^k^JHFRAT: John Hopkins Fall Risk Assessment.

^l^CSI+: Caregiver Strain Index plus.

^m^CarerQoL-7D: Care-related Quality of Life.

^n^CarerQoL-VAS: Care-related Quality of Life–Visual Analog Scale.

### Study Procedure

During the preoperative outpatient clinic visit, the patients and their family caregivers will be screened for eligibility and informed about the study (Table 2). If they are interested, a researcher (SM, SK, or [name]) will contact the patients after the visit to determine their preference for the study arm. If patients prefer the intervention arm, at least 2 days before hospital admission, the researcher will confirm the patients’ participation depending on the ward capacity. The FIP starts <72 hours after surgery when patients are transferred from the postanesthesia care unit to the participating surgical wards. Depending on the ward capacity and patient preferences, the program can be continued until discharge. During the follow-up period (ie, 30 and 90 days after surgery), the patient and family caregiver will be contacted by telephone by SM, SK, or [name] and asked to complete the questionnaires.

**Table 2 table2:** Study procedure.

Timing			Activity		
**Prehospital admission^a^**					
	Outpatient clinic visit	Recruitment of patients and family caregivers, screening for eligibility, and informed consent procedure Group allocation based on patient and family preferences			
	1 week before hospital admission	Patients and family caregivers from the intervention group will get access to the mobile app (so-called Mantelzorgapp)			
	2 days before admission	The researcher will confirm the patients’ participation in the intervention group depending on the ward capacity			
**Clinical phase^b^**					
	Within 24 hours after surgery	Family caregivers will receive a personalized plan based on the identified patients’ care needs, and the plan includes the personal goals of the family caregiver Goals will be documented in the electronic patient record Patients and family caregivers will complete questionnaires about their baseline characteristics			
	Day of surgery until 5 days after operation	Family caregivers start by participating in the fundamental care activities (and optional care activities) Family caregivers will register all activities in the app. Depending on the ward’s capacity and patients’ preferences, the program could be continued until discharge			
	At discharge	Patients and family caregivers will complete discharge questionnaires			
**After discharge**					
	Follow-up 30 days and 90 days after discharge	The researcher will send questionnaires to patients and family caregivers for measuring outcomes The researcher will contact the patient and family caregiver by telephone for outcome measures not mentioned in the questionnaires The researcher will collect data on the number of readmissions and complications as registered in the electronic patient record			

^a^Information about the FIP.

^b^The required clinical data regarding baseline characteristics and outcomes will be collected during hospitalization using standardized case report forms.

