### Study Setting

The study will be conducted at 5 surgical wards that provide care to patients after oncological gastrointestinal surgery in two Dutch tertiary university hospitals in the Netherlands: (1) Amsterdam University Medical Center (UMC), location Academic Medical Center (AMC) and Vrije Universiteit Medical Center, Amsterdam, and (2) University Medical Center Groningen (UMCG), Groningen. The average number of patients undergoing oncological gastrointestinal surgery as treatment for malignant pancreatic, gastric, esophageal, liver, colorectal, or peritoneal tumors in Amsterdam UMC is 415 per year and in UMCG 330 per year. Each participating surgical ward has 25 to 30 beds with a nursing:patient ratio of either 1:4 or 1:5. The participating wards were chosen because health care professionals expressed a willingness to adopt a more family-centered approach to their care.

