##### Information About Fundamental Care Activities

Family caregivers who participate in the FIP will gain access to a mobile app (so-called “Mantelzorgapp”) before patients’ hospital admission. The app has detailed descriptions of the following: (1) the rationale for performing the fundamental care activity, (2) preparation for the activity, (3) the needed material for the activity, (4) a step-by-step description on how to perform the activity, and (5) time and frequency of performing the activity. The app also includes a daily diary in which the family caregivers tick boxes if they have performed a fundamental care activity (yes or no) with writing space for comments. Furthermore, the app includes discharge information, such as whom to contact if they have concerns about patients’ health condition. The app can be downloaded without any cost from the Apple Store (Apple Inc) and Google Play Store (Google LLC) and is suitable for several mobile devices (ie, phones and tablets). If family caregivers are unable to use the app, they will receive paper-based information.

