### Outcomes

The primary patient outcome is the number of unplanned readmissions up to 30 days after surgery (Table 1). Secondary outcomes include the total number of complications at 30 and 90 days after surgery and the number of complications sensitive to fundamental care activities (eg, pneumonia, urinary tract infection, wound infection, deep vein thrombosis, malnutrition, and delirium) at 30 and 90 days after surgery. These data will be collected from patient records, and complications will be classified according to the revised version of the Clavien-Dindo classification system [37]. Secondary outcomes also include emergency department visits, ICU admissions up to 30 and 90 days after surgery, and hospital length of stay. Furthermore, patients’ QoL will be measured using the EQ-5D-5L [38], and the level of anxiety and depression in patients will be measured using the Hospital Anxiety and Depression Scale (HADS; Table 1) [39,40]. Patient satisfaction with care and sleep quality will be measured using the numeric rating scale (NRS) ranging from 0 to 10, with higher scores indicating higher satisfaction or sleep quality (Table 1). Sleep quality will be assessed once a day, from the first day after surgery until 5 days after the operation. In addition, the amount of home care (in hours per week) after discharge will be measured (Table 1). The risk screening scores routinely measured during hospital admission will be collected, ie, the Short Nutritional Assessment Questionnaire score (SNAQ) [41], the Delirium Observation Scale score (DOS) [42], the Braden scale [43], the Amsterdam UMC Extension of the John Hopkins Highest Level of Mobility scale score (AMEXO) [44] and the John Hopkins Fall Risk Assessment (JHFRAT; Table 1) [45].

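### Readmissions, the primary outcome, are read only from the electronic patient record, so unplanned admissions to other hospitals can be missed, although planned calls to both groups could pick them up

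*Protocol article*

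**What the plan says.** The Outcomes section of the protocol article defines the endpoint without reference to where the patient is readmitted: "The primary patient outcome is the number of unplanned readmissions up to 30 days after surgery".

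Table 2 (After discharge) divides follow-up data among three sources. Questionnaires are sent. The researcher will also "contact the patient and family caregiver by telephone for outcome measures not mentioned in the questionnaires". A separate sentence then deals with the primary outcome: "The researcher will collect data on the number of readmissions and complications as registered in the electronic patient record". The Outcomes section likewise takes complications from patient records.

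The Study Setting section places the wards in "two Dutch tertiary university hospitals in the Netherlands". The Study Procedure text confirms that calls to both parties are planned: "During the follow-up period (ie, 30 and 90 days after surgery), the patient and family caregiver will be contacted by telephone". There the stated purpose is completion of the questionnaires.

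No part of the article names patient report, another hospital's record, the general practitioner or a registry link as a source for readmissions.

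**The concern.** The definition is wider than the source. The endpoint is an unplanned readmission to hospital. The source is a record that, on the natural reading, belongs to the hospital that operated. A patient operated on in a tertiary centre may be readmitted to another hospital, and that event counts only if word of it reaches the record.

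Two things are at stake. If the loss is equal in the two groups, the absolute difference shrinks and power falls. If it is unequal, the primary comparison is biased. Equality cannot be taken for granted here: the Allocation section forms the groups by the preference of patients and families, so the groups may differ in where they seek care. Adjustment for baseline variables, as planned under Statistical Methods, does not repair an outcome that is recorded more completely in one group than in the other. Complications have the same stated source and the same weakness.

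**Working it through.** **Inputs from the article.** Rates of 35% (usual care) and 20% (FIP), 5% significance, 80% power, 136 per group raised to 150 (Sample Size); two-sided testing and logistic regression (Statistical Methods, Outcomes).

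**Assumed, because the article gives no figure.** The share of readmitted patients whose readmission is missed: 5% to 30%. I also assume that 35% and 20% are true rates rather than rates already observed through a record, that no event is recorded falsely, and that all 150 per group are analysed.

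**Step 1: reproduce the plan's figure.** Without continuity correction and with unpooled variance,

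n = (1.960 + 0.842)² × (0.35×0.65 + 0.20×0.80) / 0.15² = 7.849 × 0.3875 / 0.0225 = 135.2, so 136.

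The pooled-variance version gives 138. With the continuity correction that the Sample Size section names, the pooled version gives 151. So 136 is an uncorrected figure. That is a separate matter; here it means that uncorrected power is the main column below, with corrected power beside it.

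**Step 2: power with equal loss.** Observed rate = true rate × capture. With a the usual-care rate, b the FIP rate, m their mean and n = 150,

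power = Φ{ [ (a − b) − 1.960 √(2m(1−m)/n) ] / √( (a(1−a) + b(1−b))/n ) }.

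Full capture: m = 0.275; [0.15 − 1.960 × 0.05156] / 0.05083 = 0.963; Φ = 83.2%.

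20% missed: a = 0.28, b = 0.16, m = 0.22; [0.12 − 1.960 × 0.04783] / 0.04733 = 0.555; Φ = 71.0%.

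| Missed in both groups | Observed rates | Difference (points) | Odds ratio | Power, uncorrected | Power, corrected | n per group for 80% (pooled, uncorrected) |
|---|---|---|---|---|---|---|
| 0% | 35.0% v 20.0% | 15.0 | 0.464 | 83.2% | 79.7% | 138 |
| 5% | 33.25% v 19.0% | 14.25 | 0.471 | 80.5% | 76.6% | 149 |
| 10% | 31.5% v 18.0% | 13.5 | 0.477 | 77.6% | 73.3% | 160 |
| 20% | 28.0% v 16.0% | 12.0 | 0.490 | 71.0% | 66.0% | 186 |
| 30% | 24.5% v 14.0% | 10.5 | 0.502 | 63.7% | 58.0% | 221 |

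Equal loss hardly moves the odds ratio. What it costs is power and absolute difference.

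**Step 3: unequal loss.** This is also an illustration, with no supporting figure in the article.

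- Capture 80% in usual care and 90% in FIP: 0.35×0.80 = 28.0% v 0.20×0.90 = 18.0%, a difference of 10.0 points; odds ratio (0.18/0.82)/(0.28/0.72) = 0.56.
- Capture 90% in usual care and 80% in FIP: 31.5% v 16.0%, a difference of 15.5 points; odds ratio (0.16/0.84)/(0.315/0.685) = 0.41.

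The true values would be 15.0 points and 0.46. The error can go either way.

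**The case against.** The strongest case against is that the article does not establish the loss. It does not say whose record is read, whether letters from other hospitals are filed in it, or what the callers ask. A condensed article may leave such details to the full protocol. The telephone wording could be stretched to cover readmissions. The 35% and 20% come from the team's own pilot; if the pilot also counted from records, they are already observed rates, and applying a capture fraction would count the loss twice. At the mild end, with 5% missed, uncorrected power is still 80.5%. The record also has a merit: it does not depend on response, whereas the Sample Size section expects 10% to 20% not to complete questionnaires.

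Most of this stands as a limit on size. It does not remove the point, because the source is stated and not merely left out: the sentence after the one on telephone contact gives readmissions to the record.

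A reader might go further in four ways that the documents do not support.

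- *The app steers FIP patients back to the study hospital.* The app does hold "discharge information, such as whom to contact if they have concerns", but the article does not describe the discharge advice given in usual care, so a contrast between the groups is conjecture.
- *Emergency department visits are affected in the same way.* Table 2 assigns only readmissions and complications to the record and names no source for emergency visits.
- *Power collapses.* That needs a large gap in capture between the groups, for which there is no figure.
- *The error cannot be repaired afterwards.* Letters from other hospitals filed in the record may recover some of the events.

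**Conclusion.** The point holds as a mismatch between a definition that covers any hospital and a source that, on the natural reading, covers the study hospitals. Followed as written, the plan can miss primary-outcome events, and the preference design gives no assurance that the loss is equal.

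The size is unknown. If the planning rates are true rates and 5% to 30% are missed equally, power at 150 per group is between about 80.5% and 64%, against 83% with full capture. If those rates already reflect record-based counting, the power loss is smaller or absent, but the possibility of unequal capture remains. Neither the direction nor the size of any bias can be read from the article. The point deserves action because it touches the primary outcome and the remedy uses contacts already planned for both groups.

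**What to change.** **In the plan.** In Table 2 (After discharge), make the source of readmissions the electronic patient record plus the 30- and 90-day telephone contact. Ask both groups the same fixed question: any unplanned admission to any hospital, with date and reason. Verify reported events where possible. Count them by the window that runs from surgery. The date is essential, because the Study Procedure text times the calls from surgery while Table 2 times follow-up from discharge; these two should be reconciled. Report per group the number of events found only by telephone, and give a record-only sensitivity analysis.

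**Now.** The Results section says that follow-up ended in May 2022. If the calls did ask about admissions elsewhere, one sentence saying so settles the matter. If they did not, check outside correspondence in the record by the same procedure in both groups, add the events found, keep the record-only analysis beside it, and state the remaining limitation in the results paper.

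**Cost.** One question in calls already planned, or a letter check for about 300 patients. Self-reports need verification of date and reason. Response to the calls may also differ by group and so bring in unequal capture of its own, which is why the record-only analysis is kept.

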### Allocation

Participation in the FIP is based on the preferences of patients and, if available, their family caregivers. This means that when the patients and their relatives want to participate in the program, they will be allocated to the intervention group and when the patients or their relatives do not want to participate in the program (but give consent for observation in the usual care group), they will be allocated to the usual care group. By using this patient preference study design, we might introduce contamination between the intervention and comparison groups, as patients in the comparison group might learn about fundamental care activities and adopt them themselves or receive informal care without the program. Nevertheless, this study design was selected deliberately because no clear signs of contamination were observed between the study groups in the pilot study [16]. To minimize the risk of between-group contamination, the information for patients and their families before inclusion will not include detailed information about the fundamental care activities that comprise the program.

### Sample Size

The sample size is based on the primary objective of evaluating the effects of the FIP on unplanned readmissions. In our pilot study, we found an absolute reduction of unplanned readmission rates of 15% [16] and considered this 15% reduction of unplanned readmissions as clinically relevant, representing a readmission rate of 20% in the intervention group and 35% in the usual care group. To detect a 15% reduction in readmission rates at a 5% significance level (α) and a power of 80% (1 – β), a sample size of 136 patients per group is necessary, using a continuity-corrected chi-square test. We assume a 10% to 20% loss to follow-up (ie, not completing the questionnaires), and to compensate for this, the total sample size per group will be at least 150. Loss to follow-up is expected owing to the use of repeated questionnaires, which may burden patients. Recruitment ends as soon as both the groups have included 150 patients. To minimize attrition, we will collect detailed contact information and offer patients alternative data collection methods such as paper-based questionnaires if patients do not have an email address [52].

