**Methods:**

This cohort study will be conducted in 2 academic hospitals in the Netherlands. The FIP will be offered to adult patients and their FCs. Patients are scheduled for oncological gastrointestinal surgery and have an expected hospital stay of at least 5 days after surgery. FCs must be willing to participate in fundamental care activities during hospitalization and after discharge. Consenting patients and their families will choose to either participate in the FIP or be included in the usual care group. According to the power calculation, we will recruit 150 patients and families in the FIP group and 150 in the usual care group. The intervention group will receive the FIP that consists of information, shared goal setting, task-oriented training, participation in fundamental care, presence of FCs during ward rounds, and rooming-in for at least 8 hours a day. Patients in the comparison group will receive usual postoperative care. The primary outcome measure is the number of unplanned readmissions up to 30 days after surgery. Several secondary outcomes will be collected, that is, total number of complications (sensitive to fundamental care activities) at 30 and 90 days after surgery, emergency department visits, intensive care unit admissions up to 30 and 90 days after surgery, hospital length of stay, patients’ quality of life, and the amount of home care needed after discharge. FC outcomes are caregiver burden and well-being up to 90 days after participating in the FIP. To evaluate fidelity, we will check whether the FIP is executed as intended. Univariable regression and multivariable regression analyses will be conducted.

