#### Outcomes

Univariable regression and multivariable regression analyses will be conducted using stepwise backward selection. For the primary outcome (ie, unplanned readmissions up to 30 days after surgery), we will conduct logistic regression analyses. For continuous secondary outcomes, we will use linear regression analyses; for dichotomous outcomes, we will use logistic regression analysis. We will use a general linear mixed model to analyze differences in sleep quality, DOS scores, and AMEXO scores over 5 days after the operation (Table 1). If a difference is observed, a post hoc power analysis will be used to examine which time point differs significantly. A 2-sided *P* value ≤.05 will be considered statistically significant. A 95% CI for the beta coefficient (β) will be calculated.

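### The 136 per group is not a continuity-corrected sample size (that is 151), and 150 per group does not cover the stated 10% to 20% loss, so the stated assumptions do not give 80% power

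*Protocol article*

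**What the plan says.** The Sample Size section of the protocol article sizes the study on unplanned readmissions. It takes a 15-point absolute reduction, "representing a readmission rate of 20% in the intervention group and 35% in the usual care group", with 5% significance and 80% power, and concludes that "a sample size of 136 patients per group is necessary, using a continuity-corrected chi-square test".

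It continues: "We assume a 10% to 20% loss to follow-up", explained in brackets as failure to complete questionnaires. To compensate, "the total sample size per group will be at least 150". Recruitment stops once both groups have 150 patients. The Methods paragraph of the abstract repeats the target: "According to the power calculation, we will recruit 150 patients and families in the FIP group and 150 in the usual care group".

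Two other places bear on this:

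- The Outcomes subsection of Statistical Methods fixes the sidedness ("A 2-sided *P* value ≤.05 will be considered statistically significant") and names logistic regression for the primary outcome.
- Table 2, under the heading for the period after discharge, gives the source of the primary outcome: "The researcher will collect data on the number of readmissions and complications as registered in the electronic patient record".

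**The concern.** The paragraph prints event rates, an error rate, a power, a named test, a sample size, a loss range and an enrolment target. These should follow from one another, and at three points they do not:

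- **Test and number.** A continuity correction adds about 2 divided by the difference in proportions to each group, here roughly 13 patients. A figure as low as 136 suggests that no correction was applied.
- **Loss and target.** Going from 136 to 150 is too small a step for a loss of 10% to 20%.
- **Loss and endpoint.** The sample for a record-based outcome is inflated for missing questionnaires, which need not remove anyone from that outcome.

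At stake is the power claim for the primary outcome. If the study finds no difference, readers will weigh that result against 80% power, which the printed assumptions do not support.

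**Working it through.** **Inputs.** Rates 0.35 and 0.20 (difference 0.15), α = 0.05, power 80%, equal groups, loss 10% to 20%, all from Sample Size. Two-sided testing is from Statistical Methods, Outcomes. The normal quantiles are 1.960 and 0.8416, and (1.960 + 0.8416)² = 7.849.

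**1. Reproducing 136 (no correction)**

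- Unpooled variance: n = 7.849 × (0.35×0.65 + 0.20×0.80) / 0.15² = 7.849 × 0.3875 / 0.0225 = 135.2, so 136. This is the printed figure.
- Pooled variance under the null (mean rate 0.275): n = [1.960 × √(2×0.275×0.725) + 0.8416 × √0.3875]² / 0.0225 = 137.9, so 138.

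**2. Applying the continuity correction**

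n_cc = (n/4) × [1 + √(1 + 4/(n × 0.15))]²

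- From 137.9: (137.9/4) × [1 + √1.1934]² = 150.95, so 151.
- From 135.2: (135.2/4) × [1 + √1.1973]² = 148.2, so 149.
- Other corrected two-sided versions: 149.8 (arcsine) and 152.1 (pooled variance in both terms).
- Corrected one-sided version: 122.

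No corrected version gives 136. Against 151 the gap is 15 per group, about 11%.

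**3. Allowing for loss**, n / (1 − loss)

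| Evaluable per group | 10% loss | 20% loss |
|---|---|---|
| 136 | 151.1 → 152 | 170 |
| 151 | 168 | 189 |

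An enrolment of 150 leaves 150 × 0.9 = 135 or 150 × 0.8 = 120, both below 136. The loss that 150 can absorb is 1 − 136/150 = 9.3%, which lies outside the stated range. Multiplying instead of dividing gives 136 × 1.1 = 149.6, which may be where 150 came from; the protocol does not say.

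**4. Exact power at 35% versus 20%** (full binomial enumeration, two-sided 5%)

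| Analysed per group | Continuity-corrected chi-square | Uncorrected chi-square |
|---|---|---|
| 120 (20% loss) | 70.0% | 74.7% |
| 135 (10% loss) | 75.2% | 79.6% |
| 136 | 75.7% | 80.0% |
| 150 (no loss) | 79.9% | 83.5% |
| 151 | 80.3% | 83.8% |

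The row for 136 confirms step 1: 136 per group gives 80% power without the correction and 75.7% with it.

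**The case against.** The strongest reply is that the corrected chi-square is not the planned primary analysis. Statistical Methods specifies logistic regression, which has no continuity correction. By the same enumeration, an unadjusted logistic likelihood-ratio test has power 80.0% at 136, 83.5% at 150, 79.6% at 135 and 74.9% at 120 per group. On that view 136 suits the unadjusted planned analysis and only the label is wrong.

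Second, the stated loss is questionnaire non-completion and readmissions are taken from the patient record. All 150 per group may therefore be analysed, giving about 80% power even with the correction. The 70% to 75% range and the enrolment of 168 to 189 apply only if the loss reaches the primary outcome.

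Third, at 10% loss the shortfall from 136 is two patients per group (152 against 150); it is material only towards 20%, where it is 20 per group. Follow-up has also ended, so no recruitment decision depends on the point.

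All of this is correct, and it limits the practical weight. It does not make the printed number, test and loss agree. The section sizes the primary outcome, applies the loss to it and says that 150 compensates, which it does not at any loss from 10% to 20%, whichever test was meant. The argument that rescues the design, a complete record-based outcome, is not the one the section makes.

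**Conclusion.** The concern holds. The 136 per group is an uncorrected figure labelled as continuity-corrected; the corrected requirement is 151 (148.2 to 152.1 before rounding, depending on the variance formula). The target of 150 falls short of the protocol's own 136 after loss by 2 per group at 10% and 20 per group at 20%. Taken as written, with the corrected test and 10% to 20% loss, power is 75.2% to 70.0% instead of 80%.

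This rests on the protocol's rates of 35% and 20%, two-sided testing, equal groups and an unadjusted comparison. The power shortfall further requires that the stated loss applies to readmissions, as the section treats it. If readmissions are known for all 150 per group, power is 79.9% with the correction and 83.5% without, and what remains is a wrong justification for an adequate size.

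**What to change.** Correct the Sample Size text, and the abstract's reference to the power calculation where needed, without changing enrolment:

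1. Either describe 136 per group as the result without continuity correction, or keep the correction and give 151. Since the primary analysis is logistic regression, the first is simpler. State there that the calculation is two-sided.
2. State that 150 per group gives about 80% power (corrected) or 83.5% (uncorrected) if the record-based readmission outcome is complete. For 10% to 20% loss on that outcome, give 75.2% to 70.0% (corrected) or 79.6% to 74.7% (uncorrected).
3. Apply the questionnaire loss to the questionnaire outcomes only, and say separately what loss, if any, is expected for readmissions.
4. Remove the claim that 150 compensates for 10% to 20% loss.

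The cost is a few sentences and a slightly less favourable power statement. No data collection or analysis changes.
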